## 2. Materials and Methods

### 2.1. Study Design

This study will use a cluster randomized controlled trial design, with the community as the unit of randomization and various interventions, to evaluate the effectiveness of IMB-based behavioral intervention and conditional economic incentives among the Chinese older adults. The primary outcome is influenza vaccination over the follow-up durations.

We will choose communities from different provinces where the influenza vaccine is not covered by the present health system and older adults needs to pay out of pocket. In the two targeted provinces (Jiangsu and Shandong), four communities will be selected from urban and rural areas within each province, resulting in eight communities in total. These eight communities will be stratified based on their urban or rural status and then randomly allocated to (1) the IMB-based behavioral intervention group, (2) the conditional economic incentives group, (3) the combined IMB-based behavioral intervention and conditional economic incentives group, and (4) the control group. We will assess influenza vaccine uptake before and after the intervention and between different study arms. Figure 1 illustrates the study design.

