### 2.3. Sample Size and Sampling

The primary outcome in this study is the influenza vaccination rate among older adults, assuming a two-sided test, a type I error rate (α) of 0.05, and a type II error rate (β) of 0.10. Based on a literature review, the current median influenza vaccination rate among older adults is 8% in China at national level [10], and the target vaccination rate after the IMB-based behavioral intervention is set at 16%. Accounting for the cluster sampling approach (with a design effect between 1.3 and 1.5), the required sample size per group is 72, for a total sample size of 576 participants. Assuming a 10% loss to follow-up in the final assessment, the total sample size is 640 participants, with 160 participants per arm, across two provinces and eight communities.

The client list of Essential Public Health Services in each community health service center will be used to facilitate participant randomization and recruitment. Within each participating community, a simple random sampling approach will be used to recruit 80 participants using computer-generated random numbers. All screening and recruitment will be carried out by the local staff working at the community health service center.

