### 2.7. Data Analysis

The mean and standard deviation will be used to describe the data for numerical variables such as intention to be vaccinated and scores on each element of the IMB model. The *t*-test will be used to compare the balance of baseline data between the intervention group and the control group for these variables. For categorical variables such as influenza vaccination, the rate will be used to describe the data, and the chi-square test will be used to compare the balance of baseline data between the intervention group and the control group.

We will estimate the Difference in Differences (DIDs) (with a 95% confidence interval (CI)) of the proportion of vaccine uptake between each intervention and control (non-intervention) arm, adjusting for the clustering effect and testing whether it is statistically significant or not at a 5% level of significance. This study will use mixed-effects models to evaluate the impact of the primary and secondary outcome indicators. A generalized mixed linear model will be used to assess the impact of categorical outcome variables, and a mixed linear model will be used to evaluate the effect of continuous outcome variables. The effect evaluation process will follow the intention-to-treat principle. All statistical analyses will be performed using IBM SPSS Statistics (version 27) and SAS (University Edition, version 9.4). The statistical significance level will be *p* < 0.05.

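### With two communities per arm, the 5% difference-in-differences test rests on 4 between-community degrees of freedom (3 with the stratum), and large-sample mixed-model inference would put its type I error at about 5–11%

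*Protocol article*

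**What the plan says.** Section 2.1 fixes the number of randomised units: "four communities will be selected from urban and rural areas within each province, resulting in eight communities in total". These are allocated to four arms with stratification by urban or rural status, so each arm has two communities (one urban and one rural if the strata are balanced).

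Section 2.7 fixes the inference. The difference-in-differences in uptake between each intervention arm and control is to be estimated with a 95% confidence interval, "adjusting for the clustering effect and testing whether it is statistically significant or not at a 5% level of significance". The method is stated as "This study will use mixed-effects models to evaluate the impact of the primary and secondary outcome indicators", with a generalised model for binary outcomes. SPSS and SAS are named. The estimation method, the random-effect structure and the reference distribution are not.

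Section 2.3 gives the only information on clustering, "with a design effect between 1.3 and 1.5", with 80 participants recruited per community. No ICC is given.

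**The concern.** Treatment is assigned to communities, so the evidence against chance comes from how communities within an arm differ. With eight communities and four arm means there is very little of it. Two things follow.

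- **Variance estimated from few units.** A mixed model must estimate the community variance from 4 degrees of freedom, and the estimate is often zero. If a normal reference (critical value 1.96) is then used, the uncertainty in that variance is ignored.
- **The contrast is a before-after one.** A community intercept enters both seasons and largely cancels from the change within a community. What remains is community-by-season variation. If the model has no term for it, the standard error is close to that of independent participants. The Discussion itself expects vaccination promotion policies to differ between regions. If they also change between seasons, an intercept cannot absorb that.

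At stake are the p-values and intervals for the primary comparisons: ordinary differences between two pairs of communities could be reported as an intervention effect.

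**Working it through.** **Inputs**
- 8 communities, 4 arms, 80 per community, 160 per arm (Sections 2.1 and 2.3).
- Uptake 8% under control and 16% as target; two-sided 0.05 and 90% power (Section 2.3).
- Design effect 1.3–1.5 (Section 2.3).
- Assumptions not in the article: equal community sizes, beta-binomial or logistic-normal community effects, and the share of clustering that is stable between seasons.

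**The plan's own figures.** No actual error rate is stated beyond the nominal 5%. The sample-size arithmetic 72 × 8 = 576 and 576/0.9 = 640 reproduces. The 90% power does not: 8% versus 16% needs 345 per arm before clustering, and 345 × 1.3 to 345 × 1.5 = 449 to 518 after it, against 144 per arm (72 × 2). That is a separate matter, but it bears on the power figures below.

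**Degrees of freedom.** 8 − 4 = 4, or 8 − 4 − 1 = 3 with the stratum. Critical values are 2.78 and 3.18 instead of 1.96. Ratios: 2.78/1.96 = 1.42 and 3.18/1.96 = 1.62.

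**Implied ICC.** (1.3 − 1)/79 = 0.0038 and (1.5 − 1)/79 = 0.0063.

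**If clustering were ignored.** 2·P(Z > 1.96/√1.3) = 8.6% and 2·P(Z > 1.96/√1.5) = 11.0%.

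**Simulated type I error per comparison, logistic mixed model, Wald test at 1.96**

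| Model | Design effect 1.3–1.5 |
|---|---|
| Post-intervention only, REML pseudo-likelihood | 5.0–6.6% |
| Post-intervention only, ML (pseudo-likelihood or quadrature) | 6.4–10.0% |
| Difference-in-differences, community intercept only, all clustering community-by-season | 8.7–11.0% |
| Same, half the clustering stable between seasons | 6.4–8.2% |
| Same, 80% stable (design effect 1.5 only) | 6.8% |

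Simulation error is about 0.3 points for pseudo-likelihood (4,000 runs) and 0.6–0.8 points for quadrature (700 runs, three contrasts each).

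**Stronger clustering (assumed, post-intervention only).** ICC 0.02: REML 9–12%, ML 13–19%. ICC 0.05: REML 10–15%, ML 19–26%.

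**Community-level test.** Let s² be the variance between communities within arms, pooled over four arms. The standard error of a difference between two arm means is √[s²(1/2 + 1/2)] = s. With 200,000 null trials per setting, 8% uptake and 80 per community:
- t on 4 df, post-intervention: 5.1% at design effect 1.3 and 1.5.
- t on 4 df, before-after change with community effects independent between seasons: 4.9–5.0%.
- t on 3 df with the stratum removed: 5.0–5.1%.
- The same 4-df statistic referred to 1.96: 12.0–12.1%.
- At ICC 0.02–0.05, t on 4 df: 4.5–5.1%.

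**A t reference on the mixed model.** With 2–4 df, the mixed-model statistic rejects in only 0–1.7% of null trials at design effect 1.3–1.5.

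**Power of the community-level test, post-intervention, 8% versus 16%.** SE = √[DEFF × (0.08×0.92 + 0.16×0.84)/160] = 0.0411 at 1.3 and 0.0442 at 1.5. The non-centrality is 0.08/SE = 1.95 and 1.81. Power is 32% and 29% on 4 df, and 28% and 25% on 3 df. Simulation on 4 df gives about 25–38%, depending on uptake in the other two arms, because they contribute to the pooled variance. A z test at these design effects has about 44–49%.

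**The case against.** The strongest reply is that the article does not say large-sample inference will be used. Estimation method, degrees of freedom and random-effect structure are usual content of an analysis plan, which is not at hand, and both packages can be set up in several ways. This stands: a reader might infer that the plan rejects a small-sample correction, but the article is only silent, so the error rates above are conditional. What it does not answer is that the article itself fixes two communities per arm and promises a 5% test and a 95% interval from a mixed model. The stated design and method do not secure that level.

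A reader might also infer that a mixed model would have a true error of 12% at the planned design effect. No mixed-model variant reached that. The 12% belongs to a community-level statistic referred to the normal distribution, which the article does not propose. Nor would every p-value be too optimistic: under REML the excess for a post-intervention comparison is at most 1.6 points. That favourable case is, however, not the difference-in-differences of Section 2.7.

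Finally, it can be said that no analysis option makes up for two communities per arm. That is correct. The community-level test restores the level but not the power.

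**Conclusion.** The concern holds in conditional form. With two communities per arm, the planned test rests on 4 between-community degrees of freedom (3 with the stratum), and the article states nothing that accounts for it. With large-sample inference the type I error per comparison is about 5–11% at design effect 1.3–1.5. Where it falls depends on estimation and on whether community-by-season variation is modelled. The 10–26% at ICC 0.05 is a sensitivity figure: that ICC is not in the article and corresponds to a design effect of 1 + 79 × 0.05 = 4.95.

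It would also be tempting to treat a mixed model with few-degrees-of-freedom inference (Kenward–Roger or between-within) as an equal remedy. The check does not support that, since a between-community t reference on the mixed model made the test very conservative at this design effect. The community-level t test is the better primary analysis because it holds close to 5% across the ICCs tried.

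**What to change.** In Section 2.7:

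1. Make the primary test a community-level analysis. For each community, compute the before-after change in uptake; compare arm means of these changes; pool the variance over all four arms; refer to t on 4 df, or 3 if the stratum is fitted. Give the 95% intervals on the same degrees of freedom.
2. If a mixed model is kept as a supporting analysis, include a community-by-period random effect, and note that a few-df t reference on it is conservative at this design effect.
3. State that each pairwise comparison rests on two communities per arm.

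This needs new analysis wording and no new data, and should be settled before outcomes are seen. The price should be stated openly: for the same standard error, intervals are about 1.4–1.6 times as wide as with 1.96. Power for a post-intervention comparison of 8% versus 16% is roughly 25–38% on 4 df (somewhat less on 3), against the planned 90%. Much of that gap is already there with a z test (44–49%). Power for the before-after change also depends on the correlation between seasons, which the article does not give. Only more communities per arm would recover power.

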### 2.8. Data Management

Researchers will input data from participants’ original observation records into the study subject record forms, and the completed survey forms will be promptly submitted to the research data manager. Data entry will be performed using a dual-entry database system and will undergo two rounds of comparison. If any issues arise during this process, the researchers will be required to provide explanations. Once all subject record forms have been entered twice and verified without errors, the data manager will generate a database check report. This report will include information on study completion (including a list of dropouts), eligibility/exclusion criteria checks, integrity checks, logical consistency checks, outlier data checks, time window checks, and adverse event checks. The data files, including the database, validation programs, analysis programs, results, codebooks, and explanatory files, will be categorized and kept private using a unique identification number. Participants’ data privacy will be ensured, and all data collected throughout the research will be kept strictly confidential and will not be shared with anyone else. Also, there will be strong controls on who has access to the data forms and rigorous adherence to maintaining data confidentiality. There will be no sharing of participant names or any other identifying information.

### 2.9. Quality Control

Rigorous quality control measures will be implemented throughout the research process. Detailed work plans, implementation manuals, subject record forms, and informed consent forms will be developed and subjected to rigorous ethical review for approval. We will establish training and assessment programs for all research personnel to ensure a uniform understanding of inclusion/exclusion criteria, standardize data recording procedures, and maintain a consistent outcome assessment. A pre-study pilot test involving at least 40 participants will be conducted to refine study procedures and identify potential issues before the main study commences. Any participant who withdraws from the study before completing the prescribed observation period will be designated a dropout. Researchers will actively seek contact with dropout subjects to document reasons for the last intervention date and complete as many assessments as feasible. Additionally, all dropout subjects’ records will be retained for analysis.

## 3. Discussion

This randomized controlled trial protocol outlines a study aimed at enhancing influenza vaccination uptake among the Chinese older adults through a multifaceted approach combining Information–Motivation–Behavioral Skills (IMB) model-based behavioral interventions and conditional economic incentives. This research addresses the pressing public health issue of low influenza vaccination rates in older adults, who are particularly susceptible to severe complications.

The IMB model, a well-established theoretical framework that has shown promise in altering health behaviors, could provide empirical evidence on the effectiveness of behavioral interventions. The IMB model-based intervention focuses on enhancing older adults’ knowledge of influenza vaccines, motivating them to protect themselves against influenza and improving their behavioral skills to carry out the vaccination act. Interventions guided by this model address various barriers to influenza vaccination, including lack of awareness, insufficient motivation, and obstacles related to accessing vaccination services [33].

This study will further verify whether increasing economic incentives can further improve the effectiveness of the intervention. Economic incentives leverage the power of extrinsic rewards to stimulate behavioral changes, potentially overcoming financial barriers and reinforcing positive vaccination behaviors [41]. The inclusion of economic incentives is an innovative strategy that capitalizes on the potential of monetary rewards to motivate individuals toward health-promoting actions [23]. By analyzing objective vaccination records from community health service center databases and assessing the distinct and combined effects of these interventions, this study will provide valuable insights for shaping policies and practices aimed at promoting influenza vaccination among older adults in China.

Several practical and operational issues should be addressed to ensure the trial’s effectiveness and feasibility. First, to ensure a reasonable response rate and follow-up rate, we will provide participants with clear, easy-to-understand informational materials and ensure that follow-up procedures are streamlined and that participants receive reminders via multiple channels. Second, to ensure the study’s quality, we will provide standard training to all staff involved in participant recruitment and filing work. Third, to establish an objective measure of our primary outcome of vaccination status, we will obtain official vaccination records that will be provided and certified by the local health authorities (instead of self-reported data from our participants). Last, quality control measures will be instituted throughout the whole study process to monitor adherence to protocols and ensure consistency in data collection.

This study has several potential limitations. Firstly, its generalizability may be limited due to its focus on self-paid influenza vaccination within specific communities in China. However, existing research suggests that even in regions with free influenza vaccination, uptake rates remain low [42]. The behavioral interventions and economic incentives explored in this study hold promise for enhancing vaccine acceptance and uptake. Secondly, the effectiveness of economic incentives could be influenced by external factors, such as changes in the financial environment or variations in individual preferences for monetary rewards. To mitigate this bias, we consider affordability as a moderating variable in vaccine uptake. Additionally, given the varying influenza vaccination promotion policies across different regions, the study is subject to overestimating or underestimating the intervention effects. Lastly, it is important to note that the study duration might not fully capture the long-term sustainability of the observed effects. Future research could explore the adaptability of the IMB model and economic incentives in different cultural and economic contexts to provide more generalizable findings.

## 4. Conclusions

This study presents a research design to address the critical issue of low influenza vaccination rates among Chinese older adults. By combining behavioral interventions grounded in the IMB model with conditional economic incentives, we seek to identify effective strategies to significantly improve influenza vaccination uptake in this high-risk population. The findings of this study will have important implications for public health policy and practice, as well as for future research in this field.

## Figures and Tables

**Figure 1 healthcare-12-02361-f001:**
[figure not shown]
Schematic diagram of study method.

**Figure 2 healthcare-12-02361-f002:**
[figure not shown]
The theoretical framework for influenza vaccination cognition and behavior among older adults in China.

## Data Availability

No new data were created or analyzed in this study.
